## LIST OF ABBREVIATIONS AND DEFINITIONS

| Abbreviation | Definition                                              |
|--------------|---------------------------------------------------------|
| ACIP         | Advisory Committee on Immunization Practices            |
| ACOG         | The American College of Obstetricians and Gynecologists |
| AE           | Adverse Events                                          |
| BMI          | Body Mass Index                                         |
| CDC          | Centers for Disease Control and Prevention              |
| CI           | Confidence Intervals                                    |
| COPD         | Chronic Obstructive Pulmonary Disease                   |
| CPMP         | Committee for Proprietary Medicinal Products            |
| CRF          | Case Report Form                                        |
| EC           | Ethics Committee                                        |
| EMA          | European Medicines Agency                               |
| EU           | European Union                                          |
| GBS          | Guillain-Barre syndrome                                 |
| GCP          | Good Clinical Practice                                  |
| GDM          | Gestational Diabetes Mellitus                           |
| GMT          | Geometric Mean Titer                                    |
| GMTR         | Geometric Mean Titer Ratio                              |
| HA           | Hemagglutinin                                           |
| HAI          | Hemagglutination Inhibition                             |
| ICH          | International Conference on Harmonisation               |
| IEC          | Independent Ethics Committee                            |
| IRB          | Institutional Review Board                              |
| MedDRA       | Medical Dictionary for Regulatory Activities            |
| RNA          | Ribonucleic acid                                        |
| SAE          | Serious Adverse Events                                  |
| SOC          | System Organ Class                                      |
| URI          | Upper respiratory illness                               |
| WHO          | World Health Organization                               |

## 1. INTRODUCTION

Influenza, commonly called "the flu," is an illness caused by RNA viruses that infect the respiratory tract of many animals, birds, and humans. In most people, the infection results in the person getting fever, cough, headache, and malaise (tired, no energy); some people also may develop a sore throat, nausea, vomiting, and diarrhea. The majority of individuals has symptoms for about one to two weeks and then recovers with no problems. However, compared with most other viral respiratory infections, such as the common cold, influenza (flu) infection can cause a more severe illness with a mortality rate (death rate) of about 0.1% of people who are infected with the virus.

Pregnant women, even those who are healthy, can become very sick if they get the flu (influenza). For example, one large study reported in 1998 documented the serious impact that flu can have during pregnancy. [1] This study examined the effect of the flu on pregnant women over 17 previous flu seasons. It found that during the flu season, pregnant women in the third trimester were just as likely to be hospitalized for heart or lung problems as women with serious, chronic medical conditions who were not pregnant. The risk increased the farther along the women were in their pregnancies. Healthy women at 37 to 42 weeks were almost five times as likely to be admitted to the hospital during the flu season for heart or lung problems as women who were one to six months postpartum. Another study showed that pregnant women with asthma in particular were at high risk for hospitalization during the flu season. [2]

Because of these findings, the U.S. Centers for Disease Control and Prevention (CDC) recommend that women who are or will be pregnant during the flu season get the flu vaccine. [3] The American College of Obstetricians and Gynecologists (ACOG) concurs with this recommendation. [4]

Experts believe that the flu vaccine will provide protection against the flu in pregnant women (as it does in healthy adults) although earlier observational research could not confirm this. [5] However, a more recent experimental study from Bangladesh suggests protection against the flu for both the mother and infant when the mother was vaccinated against the flu. [6]

Because the flu vaccine is an inactivated vaccine (containing no live virus), vaccine experts believe it to be safe for pregnant women. An early study of the flu vaccine in more than 2,000

pregnant women revealed no excess malignancies in the fetus. [7] A similar but smaller study revealed no harmful effects of the flu vaccine on the fetus or the mother. [8] More recent research found no serious adverse effects from the flu vaccine in the perinatal period or during the first six months of infant life. [9] Although the numbers of patients in these studies are relatively small, these results are reassuring.

According to the previous result, in the season of 2010-2011, the adults (aged between 20 and 60) had the seroprotection rates (HAI titer  $\geq 1:40$ ) were 92.1% against influenza A/H1N1 virus, 85.7% against influenza A/H3N2 virus and 44.4% against influenza B virus 3 weeks after vaccination. The seroconversion rates were 79.4% against influenza A/H1N1 virus, 68.3% against influenza A/H3N2 virus and 28.6% against influenza B virus.

Moreover, 68.3% were females. Among these 43 female subjects, the seroprotection rates were 90.7% against influenza A/H1N1 virus, 88.4% against influenza A/H3N2 virus and 48.8% against influenza B virus 3 weeks after vaccination. The seroconversion rates were 79.1% against influenza A/H1N1 virus, 76.7% against influenza A/H3N2 virus and 34.9% against influenza B virus. Furthermore, 26 females was aged between 18~40 years old, inclusive. Among these 26 female subjects, the seroprotection rates were 92.3% against influenza A/H1N1 virus, 88.5% against influenza A/H3N2 virus and 52.8% against influenza B virus 3 weeks after vaccination. The HAI titer geometric mean fold rise was  $18.8 \pm 4.9$  against influenza A/H1N1 virus,  $14.2 \pm 5.2$  against influenza A/H3N2 virus and  $5.2 \pm 4.0$  against influenza B virus 3 weeks after vaccination. The seroconversion rates were 84.6% against influenza A/H1N1 virus, 80.8% against influenza A/H3N2 virus and 38.5% against influenza B virus.

Another trial on infants between 6 to 12 months old, 57 subjects were included to receive two vaccinations at 4 weeks apart. The seroprotection rate before vaccination were 8.8% against influenza A/H1N1, 10.5% against influenza A/H3N2 virus and 0.0% against influenza B virus. The mean HAI titer geometric before vaccination were  $6.5 \pm 2.4$  against influenza A/H1N1 virus,  $8.2 \pm 4.6$  against influenza A/H3N2 virus and  $5.2 \pm 1.2$  against influenza B virus.

A close observation of safety and immunogenicity of maternal subjects receiving an influenza vaccine may provide useful immunization strategy for preventing influenza. Consequently, this study aimed to provide immunogenicity and safety profile after receiving the study vaccine in pregnant women.

## **2. STUDY OBJECTIVES**

The purpose of this study is to evaluate the influenza vaccine (AdimFlu-S) to determine vaccine safety in pregnant women and the body's immune response.

### **2.1 Primary Objective**

- To evaluate the immune response of the three vaccine viral strains by calculation of the geometric mean titers (GMT) of anti-HA antibodies, geometric means of post- to pre-vaccination antibody titer ratios, seroprotection rates, and seroconversion rates.

The primary endpoint will be the seroprotection rate which is defined as the proportion of subjects with HAI titer  $\geq 1:40$ . The other immunogenicity endpoints include seroconversion rate and geometric mean folds increase in HAI titer. Immunogenicity profile will be assessed before vaccination, 4 weeks after the vaccination and at the end of gestation period.

Moreover, the HAI titer of the cord blood will also be measured and compared with the maternal blood sample.

### **2.2 Secondary Objective**

The secondary endpoint is to evaluate the incidence rate of pre-specified adverse events and all serious/non-serious adverse events.

### **2.3 Outcome Measure**

- Number of participants with seroprotection against influenza A/H1N1, A/H3N2, B virus (Day 28, the end of gestation period).
- Number of participants with seroconversion against influenza A/H1N1, A/H3N2, B virus (Day 28, the end of gestation period).
- Geometric means of post- to pre-vaccination antibody titer ratios against influenza A/H1N1, A/H3N2, B virus (Day 28, the end of gestation period).
- Number of participants reporting solicited subjective local reactions within 7 days (Day 1-7) post vaccination.
- Number of participants reporting solicited subjective systemic reactions within 7 days (Day 1-7) post vaccination.

- Number of participants reporting maternal complications of pregnancy, labor and delivery.
- Number of participants reporting neonatal complications.
- Number of participants reporting vaccine-associated serious adverse events (SAEs) during the study.

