### **3. STUDY DESIGN**

#### **3.1 Study Design**

This is a prospective, single-arm, descriptive clinical study to observed the safety and immunogenicity profile of the use of AdimFlu-S (2011-2012 season) vaccine in pregnant female subjects. All eligible participates will receive one dose of vaccine (0.5 mL) by intramuscular injection into the upper arm. Blood serum prepared from blood samples will be collected from each maternal subject immediately prior to vaccination and 4 weeks after vaccination; moreover, blood sample at the end of the gestation period (delivery) and the cord blood sample will also be collected, if applicable. Anti-hemagglutinin (HA) antibody titers will be determined using the WHO hemagglutination inhibition reference technique and the analysis will be observer-blinded. Safety outcomes included immediate reactions at the time of vaccination, solicited local and systemic reactions for 7 days, unsolicited adverse events until the first post-vaccination serum collected, and serious adverse events and adverse events of special interest until 8 weeks after the delivery.

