## 5.4 Schedule

The following table details the study schedule of procedures for study period:

|                              | Visit 1 |        |          | Visit 2               | Visit 3          | Follow-up              |
|------------------------------|---------|--------|----------|-----------------------|------------------|------------------------|
|                              | Week 0  | Week 1 | Week 2~3 | Week 4  | Delivery /Birth  | 8 Weeks after Delivery |
| Inform Consent               | X       |        |          |                       |                  |                        |
| Inclusion/Exclusion Criteria | X       |        |          |                       |                  |                        |
| Vital Signs                  | X       |        |          | X                     |                  |                        |
| Weight and Height            | X       |        |          |                       |                  |                        |
| Medical History              | X       |        |          |                       |                  |                        |
| Pregnancy History/Outcome    | X       |        |          |                       | X                |                        |
| Serum Samples                | X       |        |          | X                     | X  |                        |
| Dosing                       | X       |        |          |                       |                  |                        |
| Adverse Events               | X-----X |        |          |                       | X  | X        |
| Reactogenicity events        | X-----X |        |          |                       |                  |                        |
| Diary Card                   | X-----X |        |          |                       |                  |                        |
| Concomitant Medications      | X-----X |        |          |                       |                  |                        |

: The subject will return to the site for blood sampling according to her regular check-up schedule. However, the interval between the first and second blood sampling should be at least 3 weeks apart and no more than 5 weeks.

: Including maternal serum (within 8 weeks after delivery) and cord serum

: Serious adverse events and adverse events of special interest should be collected

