## 6. ADVERSE EVENTS

All reported adverse events within 4 weeks after the vaccination will be recorded as much as possible. Adverse event during the 30-minute observation period after the vaccination will be collected on site. Reactogenicity within the first 7 days after the vaccination will be recorded in the diary card. Specific adverse events of interest, i.e., Guillain-Barre syndrome, anaphylaxis, convulsions, encephalomyelitis, central nervous system demyelinating diseases, Bell's palsy and vasculitis, will also be recorded in the CRF. Moreover, influenza, pneumonia, heart failure, stroke, exacerbation of chronic pulmonary disease and other respiratory illness with fever will also be recorded.

The term "adverse event" covers any sign, symptom, syndrome or illness that appears or worsens and is not of benefit to the subject during the period of observation in a clinical study. The term also covers laboratory findings (if applicable) or the results of other diagnostic procedures considered to be clinically relevant which:

- require additional diagnostic procedures not provided for in the study protocol
- require additional treatment measures not provided for in the protocol, or
- result in withdrawal of the subject from the study.

A study-emergent adverse event is defined as any event not present prior to signing informed consent or any event already present, which worsens in either intensity or frequency after signing informed consent. A treatment-emergent adverse event is defined as any event not present prior to exposure to study vaccine or any event already present, which worsens in either intensity or frequency following exposure to study vaccine.

The investigator is responsible for reporting all study-emergent serious adverse events and all treatment-emergent non-serious adverse events. If there is any doubt as to whether a clinical observation is a study or treatment-emergent adverse event, the event should be reported.

All adverse experiences must be rated on a 3-point scale of increasing severity, which defined as below:

Mild: Symptom barely noticeable to subject; does not influence performance or functioning. Prescription drug not ordinarily needed for relief of symptom but may be given because of personality of subject.

**Moderate:** Symptom of a sufficient severity to make subject uncomfortable; performance of daily activities influenced; subject is able to continue in study; treatment for symptom may be needed.

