## **7.5 Analysis of Safety**

The safety end points are the frequency, duration, and intensity of solicited adverse events during the 7 days after each vaccination and the incidence of serious adverse events during the study period.

The Medical Dictionary for Regulatory Activities (MedDRA) Terminology will be used to classify all adverse events with respect to System Organ Class (SOC) and preferred term. In the case of severity and relationship summaries, the most severe event and the most directly related event will be presented in summary tables in the case of multiple occurrences per subject.

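### Maternal and neonatal complications are listed outcomes, but non-serious ones arising after Week 4 have no clear collection route and may be undercounted

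*Protocol*

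**What the plan says.** **Outcomes.** Protocol 2.3 lists "Number of participants reporting maternal complications of pregnancy, labor and delivery" and "Number of participants reporting neonatal complications". Neither has a definition, a seriousness threshold, a time window or a named data source. Section 2.2 sets the secondary endpoint as the "incidence rate of pre-specified adverse events and all serious/non-serious adverse events", also without an end date.

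**Adverse event collection.** Section 3.1 collects "unsolicited adverse events until the first post-vaccination serum collected, and serious adverse events and adverse events of special interest until 8 weeks after the delivery". Sections 5.1 and 5.3 follow the same split. In the 5.4 schedule, the adverse event entries at delivery and at the 8-week follow-up carry footnote (3): "Serious adverse events and adverse events of special interest should be collected". Section 6 opens with a 4-week limit: "All reported adverse events within 4 weeks after the vaccination will be recorded as much as possible". Later in Section 6, however, the investigator must report every treatment-emergent non-serious event, and the documentation paragraph sends these to the case report form. Neither sentence gives an end date.

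**Events of special interest.** The lists in 5.3 and 6 contain respiratory, cardiac, neurological and immune events. Neither names an obstetric or neonatal complication.

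**Delivery record.** Section 5.1 also records pregnancy outcome (delivery status, abortion, date or week of the event) and infant data (birth height and weight, sex, Apgar scores). Both lists are left open-ended. The 5.4 schedule marks a Pregnancy History/Outcome row at Visit 3 but not at the 8-week follow-up.

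**The concern.** Safety in pregnant women is a stated purpose of the study (Section 2), and the two complication outcomes are its pregnancy-specific part. An outcome that counts complications of any seriousness needs a collection rule that reaches events of any seriousness over the same period. Here the rule narrows at Week 4, before most women would be expected to deliver.

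If sites follow the narrower rule, mild or moderate complications arising later in pregnancy or in the infant's first weeks may not be recorded. The resulting counts could be low and be read as reassurance. If some sites follow the open-ended wording of Section 6 instead, capture would be uneven. Data not collected cannot be recovered at the analysis stage.

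**Working it through.** The protocol gives no figure to reproduce on this point, so the check sets the collection rules against the outcomes.

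**1. Which route covers which event after Week 4?**

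| Event | Adverse event rules | Delivery record (5.1; 5.4, Visit 3) |
|---|---|---|
| Serious complication, mother or infant | Covered to 8 weeks after delivery (3.1, 5.1, 5.3, 5.4) | May also appear |
| Non-serious antenatal complication, Week 4 to delivery | Outside 3.1, 5.3 and 5.4; arguably inside 2.2 and 6 | Not named |
| Non-serious labor or delivery complication | Same conflict | Delivery status named, complications not named, list open-ended |
| Non-serious neonatal finding at birth | Outside 3.1, 5.3 and 5.4 | Birth size and Apgar named, other items left to the case report form |
| Non-serious neonatal complication, birth to 8 weeks | Outside 3.1, 5.3 and 5.4 | Row not marked at the 8-week follow-up |

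Serious events are covered. Findings at delivery and birth are partly covered. The second row has no named route, and the last row has no scheduled one. One qualification: a febrile respiratory illness in an infant would count as an event of special interest under 5.3.

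**2. Is there a backup source?** Under 5.3 and 5.4, vital signs are taken at baseline and Week 4 only. Under 4.4, concomitant medications are recorded up to the second blood sample; after that, up to the end of gestation, only immunizations and immunotherapies are. Gestational diabetes, pregnancy-induced hypertension and preeclampsia are exclusion criteria in 3.3.2, so the protocol itself regards them as important. New onset after Week 4 that met no seriousness criterion would appear on no named collection list.

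**3. How much of pregnancy lies outside the non-serious window?**

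Share = (weeks from vaccination to delivery − weeks to Visit 2) / weeks from vaccination to delivery

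Inputs: Visit 2 at 4 weeks, with 3 to 5 allowed (5.1). Vaccination is allowed from 3 months, with no upper limit (3.3.1). Assumptions: 3 months is taken as 13 weeks, delivery is at 39 weeks, and 34 weeks serves as an example of late vaccination.

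- Vaccinated at 13 weeks: 39 − 13 = 26 weeks remain. (26 − 4)/26 = 85%. With Visit 2 at 5 or 3 weeks: 21/26 = 81% or 23/26 = 88%.
- Vaccinated at 34 weeks: 39 − 34 = 5 weeks remain. (5 − 4)/5 = 20%. With Visit 2 at 5 or 3 weeks: 0/5 = 0% or 2/5 = 40%.

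In these examples the share runs from 0% to 88%, depending on when a woman is vaccinated. It measures time outside the window, not events missed, because the delivery record may recover some of them.

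**4. What does one missed woman do to the result?** With all 60 planned women in the denominator, 1/60 = 1.7 percentage points.

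**The case against.** The strongest reply is that the delivery record is the intended source for these outcomes. It has no seriousness threshold, its lists are open-ended, and footnote (3) is attached only to the adverse event row, so it does not restrict the Pregnancy History/Outcome row. The case report form is not shown and may ask for complications directly. Section 6 asks for treatment-emergent non-serious events without an end date. Its seriousness criteria also bring in hospitalization, prolonged stay, congenital anomaly and medically important events, so the more consequential complications are captured up to 8 weeks after delivery.

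Most of this stands, and it rules out the reading that nothing but serious and special-interest events is collected after Week 4. It does not close the gap. The items that 5.1 names include no antenatal complication, and the delivery record is not scheduled again after birth. The open-ended sentence in Section 6 conflicts with the 4-week limit in the same section and in 3.1.

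A reader might also object that 7.5 drops these outcomes, since it names only solicited events and "the incidence of serious adverse events during the study period". Tabulating a listed descriptive outcome can be left to a statistical analysis plan, which is not at hand, so this is not a finding by itself. The same holds for restricting denominators to women still at risk at vaccination: gestational age at baseline and the date or week of the pregnancy outcome are both recorded.

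**Conclusion.** The point holds as a mismatch between listed outcomes and collection rules, together with an internal conflict over how long non-serious events are reported. Followed as written in 3.1, 5.1, 5.3 and 5.4, non-serious antenatal complications after Week 4 have no named route, and non-serious neonatal complications after birth have no scheduled one. These complications may be undercounted.

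A reader might go further and infer that they will be undercounted, or might attach a number. An assumed rate of 5% to 20% among 60 women, for example, would give 3 to 12 missed. The documents do not support that: they give no complication rate and no split by seriousness, and the multiplication presumes that the delivery record recovers nothing. The 85% share applies only near the earliest permitted vaccination.

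The conclusion rests on the protocol text; a case report form that asks for complications explicitly would reduce the problem. The immunogenicity endpoints are unaffected. The change is worth making because it is cheap and must come before data collection.

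**What to change.** Reconcile 2.3, 3.1, 5.1, 5.3, 5.4 and 6 so that they agree on what counts as a maternal or neonatal complication, where it is recorded and over what period. State one end date for non-serious event reporting that fits both 2.2 and Section 6.

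Amend footnote (3) of 5.4, with matching text in 3.1, 5.1 and 5.3, so that maternal complications of pregnancy, labor and delivery, and neonatal complications, are recorded regardless of seriousness at Visit 3 and at the existing 8-week follow-up. The Visit 3 entry should look back to Week 4, so that antenatal events are included.

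Cost: protocol wording, a case report form page if one is not already there, and slightly more data entry. No visit is added.
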